### **6.9.3.2 Viral load.**

There has been much discussion in the larger scientific community that suggests that viremic control may be a more realistic goal. It is well known, for example, that many established vaccines directly prevent morbidity and the consequences of the targeted disease without preventing infection (62).

After vaccination with various combinations of HIV vaccines, monkey challenge studies with chimeric SIV-HIV (SHIV) constructs have shown: 1) mitigation of disease rather than sterilizing immunity (reviewed in 63, 64-68); and 2) control of viremia rather than virus eradication (67,68). In humans infected with HIV there are substantial data that suggest that the level of HIV viral load shortly after resolution of acute infection is inversely correlated with disease progression (55, 56, 69-71). While it is unknown whether this would be similarly true for vaccinated individuals, animal studies using CD4 T cell loss or death as endpoints, provide further support for this hypothesis. Additionally, infectivity appears to be related to viral load, so that additional population benefits might accrue if viremia were controlled in vaccinated individuals (54,72,73).

Because of the potential advantages of a vaccine that successfully contributes to the control of viral replication, we propose to further highlight the importance of this endpoint by including viral load data in the primary analysis. This will maintain the commitment, as proposed in the study design, to ascertaining whether protection against infection occurs. Protection against infection remains a primary endpoint. Since the study size, monitoring plan, participant sampling etc. remain unchanged, this addendum only revises the way that already collected, supplementary data on viral load will be analyzed and interpreted.

To incorporate the viral load data into the primary analyses while maintaining the prior design structure, we will expand the experiment-wise error rate and include a test of viremia control. We will take advantage of the low variability, relative to the size of potentially important differences in viral load and add to the primary analysis a test for treatment differences in viral load with a two-tailed 1% Type 1 error rate. The study is adequately powered, in the absence of selection

biases, to detect half-log differences in set-point viremia. Note that the randomization principle cannot be used to validate the significance levels of comparisons between selected subgroups, that is, there may be a selection bias. For example, if the vaccine protects only those individuals who are more likely to be protected from HIV-infection or disease progression regardless of vaccination, viral loads between HIV-infected vaccine and placebo recipients may spuriously appear to be lower in the placebo group. Thus we will evaluate the vaccine causal effects, and viral load levels differences will be compared, protecting against maximal plausible selection bias (74,75).

The impact of this change will be to expand the experiment-wise Type I error rate, and it will be bounded by 6%. Thus 6% of the time, in the absence of a treatment effect, we will wrongly conclude one exists. The power of the revised final analyses is at least as great as that for the analysis used in the study design. Thus the benefits from the increased primary analysis Type I error are additional chances of claiming differences between vaccine and placebo when viral load is controlled, but infection rates are similar. A difference will be claimed when either infection-control or viremia-control occurs.

It is important to point out that results from the analysis of viral load data should be interpreted with caution. The analysis of this endpoint is a conditional analysis, since it is restricted to HIV-infected individuals, and these individuals are not a random sample from the HIV-infected population. There is a potential for selection bias since these individuals become infected post-randomization throughout the course of the study, and they are selected for the analysis because of their HIV infection status. In addition, due to the protocol-specified length of follow-up, the viral load endpoint is measured relatively early in the course of infection and limited inferences can be made about effects of vaccination on disease progression under this protocol.

Viral load measurements will be compared between HIV-infected vaccine and placebo recipients. Statistical tests will be carried out comparing the  $\log_{10}$  viral load measurements obtained after the initial diagnosis of HIV infection at the set point (Section 6.7.1). A non-parametric Mann-Whitney test will be used for the comparison. The statistical power of a t-test for differences in the  $\log_{10}$  viral load measurements between HIV-infected vaccine and placebo recipients was calculated. The calculations assume that vaccine efficacy is 25% during the immunization period and 50% after complete immunization, and that three viral load measurements are obtained on every participant who becomes infected during the trial. Detectable differences are calculated for 2-sided non-parametric Mann-Whitney tests at a significance level of 0.05. Under the anticipated study design there are expected to be approximately 43 infected vaccinees and 78 infected placebo recipients, including 10 vaccinees and 13 placebo recipients who become infected before complete immunization. Table 5 shows minimum detectable differences in  $\log_{10}$  viral load for power of 80% and 90% for varying vaccine efficacy. Detectable differences were calculated using PASS 2000 with nonparametric adjustment to a t-test. Minimum detectable differences are presented for both an intent-to-treat analysis which includes those who become infected before full immunization, and also for a per-protocol analysis which excludes those who become infected during the immunization period. If vaccine efficacy is 50% and the viral loads in the two groups differ by 0.39  $\log_{10}$  or more, then this difference should be detectable with the current study design with at least 80% power.

**Table 5.** Detectable differences in HIV-1 viral load for 80% and 90% power – intent-to-treat and per-protocol analyses.

| Type of Analysis | VE  | Infected Vaccine Recipients (#) | Infected Placebo Recipients (#) | Detectable Difference |           |
|------------------|-----|---------------------------------|---------------------------------|-----------------------|-----------|
|                  |     |                                 |                                 | 80% Power             | 90% Power |
| ITT              | 0.3 | 57                              | 78                              | 0.36                  | 0.41      |
| ITT              | 0.5 | 43                              | 78                              | 0.39                  | 0.45      |
| ITT              | 0.6 | 35                              | 78                              | 0.42                  | 0.48      |
| Per-Protocol     | 0.3 | 46                              | 65                              | 0.40                  | 0.46      |
| Per-Protocol     | 0.5 | 33                              | 65                              | 0.44                  | 0.51      |
| Per-Protocol     | 0.6 | 26                              | 65                              | 0.48                  | 0.56      |

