#### 6.9.5. Interim Efficacy Analysis (for interim safety analyses, see Section 6.9.4.1)

Under the study design assumptions, all participants will be followed for 36 months after the immunization phase with assessment for HIV infection occurring at six-month intervals. One interim efficacy analysis will be scheduled approximately 36 months after the beginning of the estimated 2-year accrual period, i.e. 36 months after the first enrollee completes the first visit. This time is estimated as the time at which the expected total patient exposure time is

approximately 2/3 of what it is expected to be at the end of the trial. Results from the interim analysis will be presented to the DSMB. The purpose of the interim analysis is to monitor the trial for early evidence of definitive efficacy. The following section outlines stopping rules assuming one interim efficacy analysis.

Two-sided O'Brien-Fleming error spending function boundary values for one interim analysis at 2/3 information time and at the end of the study period were determined using a Lan-DeMets spending function approach. Overall significance level was assumed to be 0.05. The software 'ld98.exe' that was used to calculate the values is described in Reboussin et al (60) and was downloaded from the University of Wisconsin website ([/www.medsch.wisc.edu/landemets/](http://www.medsch.wisc.edu/landemets/)). The absolute value for the two-sided O'Brien-Fleming error spending function boundary values is 2.5086 at 2/3 information time and 1.9929 at the end of the study period. If the timing of the interim analysis is changed from 2/3 information time due to practical considerations, then the boundary values will be recalculated.

The lower limit of the two-sided 95% confidence interval is used in the interim analysis to test the null hypothesis that vaccine efficacy is 30%. The method for determining repeated confidence intervals (61) draws upon the correspondence between statistical tests and confidence intervals. The lower limit of the two-sided 95% confidence interval for vaccine efficacy will be calculated as one minus the upper limit on the 95% confidence interval for the hazard ratio at the interim analyses. The upper limit of the two-sided 95% confidence interval for the hazard ratio will be determined using the O'Brien-Fleming boundary value that was computed for the analysis (i.e., 2.5086). At the interim analysis:

- If LL of 2-sided 95% CI for VE >30%, stop and reject the null hypothesis.

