The null hypothesis for the final analysis will be that true vaccine efficacy is equal to 0%. The statistical test at the planned conclusion of the trial will be a 2-sided 5% level test of the hypothesis that the risk of infection is the same at any given time in the two treatment groups. The test statistic will be compared to the O'Brien-Fleming error spending function boundary values determined for the end of the study period.

If the null hypothesis at the interim analysis is accepted and after the final analysis:

- If  $|Z_{\text{final}}| \geq 1.9929$ , reject the null hypothesis.

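### The fixed 5% + 1% split is valid but inefficient: viral load stays at 1% even after acquisition is shown, although testing it then at 5% would keep the 6% bound

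*Protocol*

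**What the plan says.** The synopsis and section 5.1 list two primary objectives: prevention of infection, and reduced viral load among those infected.

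- **Acquisition** (6.9.5). One interim and one final look, with O'Brien-Fleming spending. "Overall significance level was assumed to be 0.05". At the end, "The test statistic will be compared to the O'Brien-Fleming error spending function boundary values determined for the end of the study period", that is |Z| of at least 1.9929.
- **Viral load** (6.9.3.2). The plan will "add to the primary analysis a test for treatment differences in viral load with a two-tailed 1% Type 1 error rate". The reason given is that variability is low relative to the differences of interest.
- **Joint error** (6.9.3.2). The change will "expand the experiment-wise Type I error rate, and it will be bounded by 6" percent.
- **Success rule** (6.9.3.2). "A difference will be claimed when either infection-control or viremia-control occurs". The benefit named for the extra error is "additional chances of claiming differences between vaccine and placebo when viral load is controlled, but infection rates are similar".
- **Viral-load power** (6.9.3.2, Table 5). "Detectable differences are calculated for 2-sided non-parametric Mann-Whitney tests at a significance level of 0.05". On that basis the text claims at least 80% power for 0.39 log10 with 43 and 78 infections, and section 6.7.1 repeats the 0.39.

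Neither 6.9.3.2 nor 6.9.5 changes the level of one test according to the result of the other.

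**The concern.** The sponsor has accepted a 6% experiment-wise error. Once the acquisition null is rejected, the 5% assigned to it no longer has to be held back, yet viral load is still tested at 1%. Under the design alternative acquisition is shown about 90% of the time, so in about 90% of such trials the second primary objective is held to a level stricter than the accepted bound requires. What is at stake is the chance of a formal conclusion on viral load in a trial that has already shown an effect on infection.

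The viral-load power figures were also computed at 5%, so the text does not show the reader what the 1% level costs.

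**Working it through.** **Inputs.** 43 infected vaccinees and 78 infected placebo recipients (6.9.3.2, ITT, VE 25%/50%); acquisition power 90.2% at VE 25%/50% and 43.6% at 15%/30% (Table 4, ITT); viral-load level 1%, Table 5 level 5%. The SD of log10 viral load is not stated.

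**Method and SD.** Two-sample t power (noncentral t), with sample sizes multiplied by the Mann-Whitney efficiency 3/π = 0.955. Applied to Table 6 with its stated SD of 235, this gives 80.1% to 81.0% in the 80% column, so it matches the plan's software closely. Solving the 12 cells of Table 5 at level 5% gives SDs of 0.70 to 0.72. I use 0.71.

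**Plan's own figure.** SE = 0.71 × √[(1/43 + 1/78)/0.955] = 0.138. In the normal approximation the 80%-power difference at 5% is (1.960 + 0.842) × 0.138 = 0.39. With the noncentral t, power is 80.0% at 0.39 and 89.9% at 0.45, so Table 5 is reproduced.

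**At the level of the actual test.** The 80%-power difference at 1% is (2.576 + 0.842) × 0.138 = 0.47, or 0.48 with the noncentral t.

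| Difference (log10) | Power at 1% | Power at 5% |
|---|---|---|
| 0.39 | 58.3% | 80.0% |
| 0.50 | 84.0% | 94.9% |

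**Does 6% still hold?** Take the rule: viral load at 1%, or at 5% if acquisition has been rejected.
- Both nulls true: an error needs a false acquisition rejection (at most 5%) or a viral-load rejection at 1%. The total is at most 6%, because the 5% level is used only after an acquisition error has already occurred.
- Only the viral-load null true: at most 5%.
- Only the acquisition null true: at most 5%, because that test is unchanged.

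A stop at the interim rejects VE = 30% at 2.5086. That also rejects VE = 0%, so the bound covers it.

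**Average viral-load power at VE 50%**, treating the two results as independent:
- 0.39 log10: 0.902 × 80.0 + 0.098 × 58.3 = 78%, against 58%.
- 0.50 log10: 0.902 × 94.9 + 0.098 × 84.0 = 94%, against 84%.

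**Smaller efficacy.**
- VE 30% (57 v 78 infections): at 0.50 the gain is 0.436 × (97.5 − 90.7) = 3 points; at 0.39 it is 0.436 × (86.4 − 67.9) = 8 points. At the 0.36 in Table 5's own row it is 0.436 × (80.6 − 59.1) = 9 points.
- VE 0% (78 v 78, acquisition rejected 4.9% of the time in Table 3): at 0.39 it is 0.049 × (91.5 − 77.0) = 0.7 points.

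**Sensitivity to SD** (VE 50%, 0.50 log10). SD 0.6: 0.902 × (98.9 − 95.0) = 3.5 points. SD 1.0: 0.902 × (72.3 − 48.4) = 22 points.

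**Cost.** If VE is 50% and viral load is null, the false viral-load claim rate becomes 0.902 × 5% + 0.098 × 1% = 4.6%, against 1%.

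**The case against.** **The plan contains no error.** This stands. A fixed split is valid, the 6% statement is true, and keeping the prior design intact is a stated aim. The point is one of efficiency.

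**The 1% protects the viral-load claim.** A reader might infer that the fixed split buys no error protection at all. The documents do not support that. Only the experiment-wise bound is unaffected; the viral-load error itself is held at 1% rather than about 5% when the vaccine prevents infection. Section 6.9.3.2 warns that randomization does not validate this comparison, and selection can arise in exactly that case. As an illustration, a spurious shift of 0.1 log10 gives about 3% rejections at 1% and about 11% at 5%. In reply, the section justifies 1% by low variability, not by selection. It addresses selection with a bias-robust comparison, which the fix keeps. The power of that comparison was not computed here.

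**The either-endpoint rule is already met once acquisition is shown.** That is true, and nothing is gained in the stated target case of similar infection rates. Viral load is nevertheless a primary objective of its own.

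**Other rules may exist elsewhere.** A footnote in 6.7.1 refers to an Analytic Addendum, Section 18, which is not shown. Any different rule there would have to be reconciled with the explicit 1%.

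**Timing.** Sections 6.9.7 and 9.2 of this version already refer to trial results. A level relaxed after unblinding would not be confirmatory. This limits the use of the fix, not the assessment of the design.

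**Conclusion.** The concern holds as a point of efficiency. Viral load could be tested at 5% after an acquisition rejection without exceeding the 6% the sponsor accepted. At VE 50% this is worth about 20 points of average viral-load power at 0.39 log10 and about 10 at 0.5 log10. It is worth about 3 to 8 points at VE 30% over the same differences, and under 1 point when infection rates are equal. These figures rest on the back-solved SD of 0.71, the expected infection counts, independence of the two results, and a plain Mann-Whitney comparison at the final look. After an interim stop there would be fewer infections and less power.

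A reader might go further and test viral load at the full 6%, or re-test acquisition at 6% after a viral-load rejection. The bound would allow both, but testing a single endpoint at 6% is debatable, and the second step would contradict the two-sided 5% acquisition test in 6.9.3.1 and 6.9.5. Neither is needed.

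Separately, the claim of at least 80% power at 0.39 log10 does not describe the 1% test, whose power there is about 58%. The half-log claim does hold at 1% for ITT at VE 50% (84%).

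**What to change.** In 6.9.3.2, state that viral load is tested at two-sided 1%, or at two-sided 5% if the acquisition null has been rejected, using the selection-robust comparison already promised, with the experiment-wise error still bounded by 6%. Leave acquisition at overall 5% with the final boundary 1.9929.

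State the downside beside it: when acquisition efficacy is real and viral load is null, the false viral-load claim rate rises from 1% to about 5%. If the sponsor prefers to keep 1% throughout, give that protection as the reason.

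In 6.7.1, 6.9.3.2 and Table 5, say that 0.39 log10 applies at 5% and that at 1% the 80%-power detectable difference is about 0.48 log10, and state the SD used.

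The cost is a few sentences; no volunteers, visits or data are added. The conditional level is confirmatory only if fixed before unblinding. After that, the 1% result stands as primary and only the power statement should be corrected.

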#### **Changes in HIV-1 Viral Load**

Plasma viral load post-seroconversion is an important predictor of clinical progression of HIV infection and of transmissibility (54-56). The trial will quantitate HIV plasma viral load at the time of diagnosis and through the remainder of the follow-up period. Results will be compared in vaccine and placebo recipients who become HIV-infected during the trial. The trial is powered to detect a 0.39 log10 difference in viral load between vaccine and placebo recipients (see Section 6.9.3.2).

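### The co-primary viral-load test is set at a two-sided 1% level, but its detectable differences are computed at 5%, so the claimed 80% power at 0.39 log10 is about 59%

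*Protocol*

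**What the plan says.** Section 6.9.3.2 makes viral load part of the primary analysis by adding "a test for treatment differences in viral load with a two-tailed 1% Type 1 error rate". The stated effect is to "expand the experiment-wise Type I error rate, and it will be bounded by 6" percent, which is the 5% for infection plus 1% for viral load. A difference will be claimed if either endpoint succeeds.

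Later in the same section, the power calculation is described: "Detectable differences are calculated for 2-sided non-parametric Mann-Whitney tests at a significance level of 0.05". It assumes that "vaccine efficacy is 25% during the immunization period and 50% after complete immunization", giving "approximately 43 infected vaccinees and 78 infected placebo recipients". For a difference of 0.39 log10 at 50% efficacy the section concludes, "then this difference should be detectable with the current study design with at least 80% power".

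Section 6.7.1 carries the figure forward without a significance level: "The trial is powered to detect a 0.39 log 10 difference in viral load between vaccine and placebo recipients".

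**The concern.** The test level and the level behind the power claim differ, and both are in the current text of one section. A two-sided 1% test needs a larger difference than a 5% test for the same power, so every detectable difference in Table 5 is too small for the test specified.

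This is a primary endpoint on which the trial may claim success alone. Someone reading a null viral-load result against section 6.7.1 would believe that the trial had at least an 80% chance of finding 0.39 log10. If the true chance was nearer 60%, the null result says less than the protocol implies.

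**Working it through.** **Inputs.** Test level 0.01 two-sided, table level 0.05 two-sided, numbers infected, stated differences and method (t-test with a nonparametric adjustment) all come from section 6.9.3.2 and Table 5. The standard deviation (SD) of log10 viral load is not stated and has to be inferred.

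**Step 1: effect of the level alone, without an SD.** In the normal approximation, a difference with 80% power at two-sided 0.05 has standardized size 1.960 + 0.842 = 2.802. At two-sided 0.01 the critical value is 2.576, so

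- power = Φ(2.802 − 2.576) = Φ(0.226) = 58.9%.

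For an entry with 90% power at 0.05:

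- 1.960 + 1.282 = 3.242, and Φ(3.242 − 2.576) = Φ(0.666) = 74.7%.

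Detectable differences scale in the same way:

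- 80% power: (2.576 + 0.842) / 2.802 = 1.220, so 0.39 × 1.220 = 0.476 log10.
- 90% power: (2.576 + 1.282) / 3.242 = 1.190, so 0.45 × 1.190 = 0.536 log10.

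**Step 2: reproduce Table 5 at 5%.** I used noncentral-t power with both group sizes multiplied by the Mann-Whitney efficiency 3/π. The method was checked on Table 6, where the SD is given as 235: for 43 versus 78 it returns 129.1 against the stated 129.3. Fitting one SD to all twelve Table 5 entries gives about 0.712 log10, which matches 11 of the 12 to two decimals (largest deviation about 0.006). Table 5 is thus a correct 5% table, as its text says.

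**Step 3: same SD at 1%.** Each pair below is the 80% / 90% column.

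| Analysis, VE | Infected (vaccine/placebo) | Stated | Recomputed at 5% | Recomputed at 1% | Power at stated difference, 1% test | Power at 0.5 log10, 1% test |
|---|---|---|---|---|---|---|
| ITT 0.3 | 57/78 | 0.36 / 0.41 | 0.358 / 0.415 | 0.440 / 0.496 | 59% / 73% | 91% |
| ITT 0.5 | 43/78 | 0.39 / 0.45 | 0.391 / 0.452 | 0.480 / 0.542 | 58% / 74% | 84% |
| ITT 0.6 | 35/78 | 0.42 / 0.48 | 0.419 / 0.485 | 0.515 / 0.581 | 58% / 73% | 77% |
| PP 0.3 | 46/65 | 0.40 / 0.46 | 0.397 / 0.459 | 0.488 / 0.550 | 59% / 74% | 82% |
| PP 0.5 | 33/65 | 0.44 / 0.51 | 0.441 / 0.510 | 0.542 / 0.612 | 58% / 74% | 72% |
| PP 0.6 | 26/65 | 0.48 / 0.56 | 0.479 / 0.554 | 0.589 / 0.665 | 58% / 75% | 63% |

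**Step 4: sensitivity.** With SD 0.705 the 1% detectable differences fall by about 0.005, to 0.475 / 0.536 for the ITT 0.5 row. Power at the stated differences is then 59–60% and 74–76%. A Mann-Whitney simulation of 20,000 normal data sets (43 versus 78, difference 0.39, SD 0.716) rejects in 79% at the 5% level and 57% at the 1% level.

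**The case against.** Five points can be made for the protocol.

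- **The level is labelled.** Section 6.9.3.2 says openly that Table 5 uses 0.05, and the table is right at that level. This is true, so the fault is a mismatch with the specified test and not a slip in calculation. Section 6.7.1, however, gives 0.39 log10 with no level attached.
- **The power claim next to the 1% level is a different one.** Just after setting 1%, the section calls the study adequately powered for half-log differences. At 1% this holds for ITT at 50% efficacy (84–85%) and at 30% (about 91%). It falls to 77–78% for ITT at 60%, and to 72–73% and 63–64% per protocol at 50% and 60%. The sentence makes no per-protocol claim, so it survives as an ITT statement at moderate efficacy. It does not rescue the 0.39 figure.
- **The endpoint was added for similar infection rates.** With 78 infected in each arm, the 1% detectable difference is about 0.40 log10, and power at 0.39 is 77–78%. In that scenario the overstatement is small. But the protocol ties its 0.39 claim to 50% efficacy and 43 versus 78 infected.
- **Interpretation is already guarded.** Section 6.9.3.2 urges caution with viral-load results, and the futility rule in section 6.9.6 uses a 99% confidence interval. The cautions concern selection bias and early measurement, not power, and the 99% interval confirms that 1% is the intended scale.
- **An Analytic Addendum exists.** A footnote to section 6.7.1 refers to Section 18 for the primary analyses, and that section is not in the text at hand. It may hold 1% calculations, but sections 6.7.1 and 6.9.3.2 would still conflict with the stated test.

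**Conclusion.** The concern holds. The power claimed for a primary endpoint is not delivered by the test that the protocol specifies. For ITT at 50% efficacy, power at 0.39 log10 is 58–59% instead of at least 80%, an overstatement of about 21 percentage points. The difference detectable with 80% power is about 0.48 log10.

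The loss of power follows from the change of level and does not depend on the unstated SD. The replacement differences do rest on an SD of 0.705 to 0.712 inferred from Table 5, and on the protocol's own assumed numbers of infections. The 1% level, the 6% bound, the choice of test and the sample size, which rests on the infection endpoint, are not affected.

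**What to change.** Recompute Table 5 at two-sided 0.01 using the sponsor's own SD, and state that SD. On the inferred SD, the ITT row at 50% efficacy becomes about 0.48 log10 (80% power) and 0.54 log10 (90%); the other rows should come close to the 1% column above. Replace 0.39 log10 in sections 6.7.1 and 6.9.3.2 with the recomputed value and give the level beside it. State the population, efficacy and power to which the half-log sentence refers.

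A row for equal infection rates (78 versus 78, about 0.40 log10) would be a useful but optional addition, since that is the situation for which the endpoint was added.

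The cost is one table and a few sentences, with a less favourable stated figure. Design, sample size and analysis stay as they are.
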